# Study protocol for the DEFENDD trial: an RCT on the Dynamic Locking Blade Plate (DLBP) versus the Dynamic Hip Screw (DHS) for displaced femoral neck fractures in patients 65 years and younger

**DOI:** 10.1186/s12891-020-3131-x

**Published:** 2020-03-03

**Keywords:** Hip fractures, Dynamic locking blade plate, Dynamic hip screw, Femoral neck fractures, Internal fixation, Gannet, Displaced, DHS, DLBP

## Abstract

**Background:**

The Dynamic Locking Blade Plate (DLBP) was recently introduced for fixation of displaced femoral neck fractures (FNF) and has been well received. Although the results of this implant in young patients are promising, the DLBP has not yet been compared to a standard device such as the Dynamic Hip Screw (DHS). The aim of this study is to compare the clinical outcome and costs of displaced FNF treated with internal fixation by means of either the DLBP or the DHS in patients up to 65 years of age. We hypothesize that the DLBP is superior compared to the DHS in terms of revision surgery rate, union rate, incidence of avascular necrosis and implant related failure.

**Methods:**

The DEFENDD (DisplacEd Femoral Neck fractures Dlbp versus Dhs) trial is a multicentre randomized controlled trial that will include 266 patients of 18–65 years with a displaced FNF. Patients will be randomized to receive either a DLBP or a DHS with a 1:1 allocation using a random block size, stratified for centre. Clinical follow up will last 1 year and questionnaires will be obtained up to 2 years. The main outcome parameter is the incidence of revision surgery within 1 year, due to either non-union, avascular necrosis (AVN) or cut out of the implant. Secondary study parameters are the incidence of avascular necrosis, non-union, (implant related) complications, functional outcome, elective removal of the implant and health-related quality of life and costs.

**Discussion:**

The outcome of the DEFENDD trial will provide high-level evidence of which implant is favourable for the treatment of femoral neck fractures in young patients (≤65 years).

**Trial registration:**

Netherlands Trial Register, NL7300 Registration date 25-09-2018.

## Background

In 1990 an estimated 1.66 million patients sustained a hip fracture worldwide. This number has increased over time and is estimated to be around 6 million in 2050 worldwide [1]. Despite these numbers the optimal treatment of hip fractures is still under debate and subsequently evolving. This especially applies to the treatment of displaced femoral neck fractures (FNFs), which differs considerably worldwide. A general consensus is that young patients (up to 65 years of age) should be treated with fracture reduction and internal fixation [2, 3]. Patients above 75 years of age are in majority treated with arthroplasty. The treatment of FNFs in young elderly (between 65 and 75 years old) is still under debate and is therefore referred to as the ‘unsolved fracture’ [4–6].

Nowadays, the most commonly used implants for fixation of FNFs are multiple cannulated parallel screws and the Dynamic Hip Screw (DHS) (Fig. 1). The DHS has a small advantage over multiple parallel screws in displaced FNFs, in that it is known to have a lower reoperation rate [8]. Despite the frequent use of both these implants the failure rate of displaced FNFs is still high, with a non-union rate of 30–33% and an incidence of avascular necrosis (AVN) of 10–16% [3, 9–11]. The reoperation rate, as a result of non-union and AVN is between the 18–48% [3, 11, 12]. The Dynamic Locking Blade Plate (DLBP) (Fig. 2), otherwise called ‘The Gannet’, is specifically designed for the surgical fixation of intracapsular hip fractures though small metal ‘wings’. The characteristics of the DLBP are its low implant volume, rotational stability, angular stability and its simple instrumentation and surgical technique. In a prospective multicenter cohort study in the Netherlands 172 patients with an undisplaced FNF were treated with the DLBP. The results of this study showed a failure rate of 4% [13]. Another recent prospective cohort study of 106 patients of 60 years and younger with displaced FNF demonstrated a DLBP related failure rate of 13.2% [14]. However, randomized controlled trials are needed to provide high-level evidence to determine the value of DLBP.

**Fig. 1 Fig1:**
[figure not shown]
The Dynamic Hip Screw [7]. Copyright by AO Foundation, Switzerland

**Fig. 2 Fig2:**
[figure not shown]
The Dynamic Locking Blade Plate with impaction anchors. Permission was given bij Gannet B.V. Hengelo for using this figure

The aim of the current study is to test if the favorable results with the DLBP persist in a multicenter randomized controlled trial for patients aged 65 years or younger with initially displaced FNFs. We hypothesize that the DLBP is superior compared to the DHS in terms of revision surgery rate, union rate, incidence of avascular necrosis and implant related failure. Also, the cost-effectiveness of the DLBP versus DHS will be assessed.

## Method/design

### Primary and secondary objectives

The primary objective is to test if the incidence of revision surgery (primary endpoint) is lower in patients ≤65 years with an initially displaced FNF treated with the DLBP in comparison to treatment with DHS. Secondary objectives are to determine the incidence of AVN, non-union, implant related complications, non-implant related complications and elective removal after fixation with the DLBP or DHS. Also, we compare operating time, functional outcome and cost-effectiveness of DLBP and the DHS.

### Study design

The DEFENDD trial (DisplacEd Femoral Neck fractures Dlbp versus Dhs) is a multicenter unblinded randomized controlled trial with a superiority design comparing two implants. One group will be treated with the DLBP. The other group will be treated with DHS (control group). The study will be performed in six trauma centers in the Netherlands. Data will be registered in Castor EDC, an online data capture program.

### Eligibility criteria

All consecutive patients between 18 and 65 years with a displaced FNF, Garden type III or IV according to the Garden classification, admitted to the participating hospitals are eligible for the study [15].

Exclusion criteria are:
Pathological fracture.Ipsilateral or contralateral fracture(s) of the lower extremity.Injury Severity Score (ISS) of ≥16.Local infection or inflammation at time of operation.Symptomatic arthritis, diagnosed by a rheumatologist.Symptomatic osteoarthritis or radiographic osteoarthritis grade III or IV [16].Previous surgery of the ipsilateral hip.Open fracture.Morbid obesity (BMI ≥ 35).Patients who were wheelchair-bound in their pre-injury situation.Patients who were, at the time of trauma, admitted to a nursing home.Patients who are not mentally competent

### Randomization

After obtaining written informed consent patients are randomized with a 1:1 allocation using a random block size, stratified for centre. Variable block sizes will be determined by the estimated inclusion number of each centre. An online randomization module is used for treatment allocation.

### Sample size calculation

The failure rate or revision rate of the DHS in patients ≤65 years with displaced FNFs described in today’s literature is 32–44% [8, 17]. The failure rate of the DLBP in patients of 60 years and younger with a displaced FNF in a previous cohort study was 13.2% [14]. Analysis of our data showed a failure rate of 15% for the DLBP in patients of 65 years and younger (non-published data). For the determination of the sample size we assumed a 30% failure rate for the DHS and 15% failure rate for the DLBP. For a power of 80% we need 121 patients per group to prove the superiority of the DLBP regarding the primary outcome (need for revision surgery) with alpha of 5% in a two-sided test. Taking into account that up to 10% of the patients may be lost to follow up, 266 patients need to be included for adequate statistical power, i.e. 133 patients per group.

### Study interventions

This trial will be performed in six trauma centres in the Netherlands. In three of the centres the DLBP will be introduced before starting this trial. In the other three participating centres the DLBP is already used. A learning curve is taken into account. The first three DLBP’s in each participating centre will be implanted under supervision of an instructor from the manufacturer or an experienced surgeon who has implanted three or more DLBP’s. The first DLBP’s of a surgeon can be included, provided that they are implanted under supervision.

### Dynamic locking blade plate

The Dynamic Locking Blade Plate consists of a 2-hole standard 135° side-plate combined with a low-volume cannulated dynamic locking blade (Fig. 2). The side plate provides angular stability combined with dynamic axial compression of the fracture. Two side wings at the tip of the blade provide rotational stable fixation of the locking blade in the femoral head combined with a high weight-bearing surface. The expandable impaction anchors lock the blade in the femoral head and prevent perforation and backing out of the implant and further augment the rotational stability. The DLBP is now marketed as the Gannet [13].

### Dynamic hip screw

The control group will be treated with the Dynamic Hip Screw, a stainless steel lag screw in the femoral neck and head that is fixated to the femur shaft with a compression plate using two-four 4,5 mm cortical screws (Fig. 1). The DHS is used globally and is provided by a wide range of commercial producers in various sizes. It can be implanted with or without an additional cannulated antirotational screw. The type of DHS used in the control group is at the discretion of the surgeon. The trauma and orthopaedic surgeons in participating trauma centres have a wide experience with internal fixation of FNF by means of DHS.

### Direct post-operative care

Both groups receive standard care including direct mobilization after surgery. Mobilization therapy will be given by a physiotherapist according to the hospital protocol for hip fracture after care. All patients receive low-molecular-weight heparin anticoagulation therapy during their stay in the hospital.

### Study procedures

A time schedule of procedures and measurements is presented in Table 1. The selection of eligible patients will take place in the emergency department (ED). According to standard care, X-ray examinations of the pelvis and hip are made on admission and assessed by the radiologist and trauma surgeon. Eligible patients will receive oral and written information about the study from the physician in the ED. The patients have at least 6 h to consider participation in the study and will be given the opportunity to ask questions about the study. Written informed consent will be obtained by the surgical resident or the surgeon after admission to the ward. Randomization will be done by the treating surgeon. After inclusion the patient will be allocated to one of the two study groups (DLBP or DHS) using an online randomization program. The baseline parameters will be registered by a nurse upon arrival on the surgical ward before surgery. The perioperative care will be the same for all included patients.

**Table 1 Tab1:** Time schedule for study procedures and measurements

	Emergency department	Admission	Post-op visit (≤5 days)	6 weeks follow-up	3 months follow-up	6 months follow-up	12 months follow-up	24 months follow-up^a^
Informed consent		x						
Baseline characteristics		x						
Radiography	x		x	x	x		x	
Questionnaires		x		x	x	x	x	x
Complications registration		x	x	x	x		x	x

^a^ Contact by telephone

Surgery will be performed by an (orthopaedic) trauma surgeon or by an (orthopaedic) trauma resident under the direct supervision of an (orthopaedic) trauma surgeon. The aim is to operate within 24–36 h based on the Dutch guidelines for treatment of FNFs [18]. After surgery, details about the surgery will be documented.

After discharge patients are scheduled for outpatient visits after 6 weeks, 3 and 12 months. Conventional radiographs will be taken and assessed during these visits (Table 1). The patients need to fill out a questionnaire before follow up visits and 6 months after discharge. Also, the patient will be contacted by telephone 24 months after enrolment in the study for additional questionnaires about mobility and complication registration.

### Study parameters

#### Primary outcome parameter

The primary outcome is the incidence of revision surgery after fixation of an initially displaced FNF treated with DLBP or DHS due to non-union, AVN or cut out of the implant. This will be monitored during 1 year of follow up after surgery.

#### Secondary outcome parameters

*Incidence of avascular necrosis*: AVN is defined as hip pain in combination with radiographical signs for AVN as described by Steinberg [19]. According to the Steinberg classification AVN is present from stage 2 and upward. AVN will be assessed by the treating surgeon. As is customary in the Netherlands, all radiographs are also assessed by a radiologist.

*Incidence of non-union*: there is no consensus in the literature regarding to the definition of (non-)union [20]. Our definition of non-union is based on the Radiographic Union Score for Hip (RUSH) [21]. Non-union is a visible fracture line on the radiograph, absence of cortical bridging or bridging trabeculae over the fracture site in combination with persisting pain in the hip and the inability to bear weight at least 9 months post-operative or sooner if revision surgery was performed because it was no longer expected that fracture healing would occur. Non-union will be assessed by the treating surgeon.

*Incidence of implant related complications:* an implant related complication is defined as breakage or cut-out of the plate or screws, inadequate expansion/malfunction of the anchors or any malfunction of the implant which may or may not lead to revision surgery. Implant related failure will be monitored during 1 year of follow up.

*Post-operative complications*: post-operative complication is defined as any unanticipated event other than the above mentioned, for which operative treatment or medical treatment is required, e.g. wound infection, bleeding or pneumonia. Every complication occurring during the hospital stay of the patient will be recorded.

*Rate of elective implant removal after union*: Elective implant removal after union will be recorded during 1 year of follow up after surgery. Reasons for elective removal will be described.

*Functional outcome:* patient-reported post-surgical function will be scored using the validated Dutch version of the International Hip Outcome Tool (iHOT-12NL) [22]. The iHOT-12NL is a patient-reported questionnaire that measures health-related quality of life and physical function in younger, active patients with hip disorders. Scores on the iHOT-12NL range between 0 and 100 (worst - best possible function). This questionnaire will be filled out by the patient during admission and at 6 weeks, 3, 6 and 12 months follow up.

*Operation time*: the operation time is recorded in the surgical report.

*Baseline parameters:* Additional parameters that will be recorded are: sex, date of birth, general health score (using the ASA classification), fracture type and side, trauma surgeon or orthopaedic trauma surgeon, type of anaesthesia, Body Mass Index. These parameters will be assessed during admission as a baseline measure.

*Costs*: Costs will be assessed from a societal perspective. Cost of (revision) surgery will be calculated using a bottom-up approach. Using a questionnaire the patients will report other health care use such as physiotherapy, rehabilitation care or nursing home care, visits to the general practitioners and medical specialists and medication, and non-medical care (domestic help and absenteeism). This questionnaire will be filled out by the patient at 6 weeks, 3, 6 and 12 months follow up. Health care use will be valued using Dutch reference prices [23].

*Health related quality of life*: the EuroQol (EQ-5D-5 L) questionnaire measures five dimensions (mobility, self-care, daily activities, pain/discomfort, anxiety/depression), on a five-point scale (no, some, moderate, much or extreme problems). For each health state described by the patients, a utility score can be calculated that reflects society’s valuation of that health state [24]. In addition, patients rate their overall health-related quality of life on a Visual Analogue scale (VAS). This questionnaire will be filled out by the patient during admission and at 6 weeks, 3, 6 and 12 months follow up. The utility scores obtained by the descriptive system and the VAS will be used in the cost-effectiveness analysis.

### Statistical analysis

Statistical analysis will be performed using SPSS (IBM Corp., Armonk, NY, USA). Primary analysis will be done according to the intention-to-treat principle. If patients are not treated according their allocated treatment a per-protocol analysis will be conducted to confirm the intention-to-treat analysis. Baseline characteristics of the treatment groups will be presented as mean with SD or as median and range for continuous variables and as number and percentage for categorical variables.

The primary outcome parameter, the incidence of revision surgery after 1 year, will be compared between the treatment groups using logistic regression analysis, including study centre as a covariate, since some study sites have used the DLBP for several years and whereas in other medical centres the DLBP has only been introduced recently. In literature there is no clear evidence of other covariates that have a strong or moderate association with the primary outcome. The secondary parameters: the incidence of AVN, non-union, implant-related complications, post-operative complications, and elective implant removal after 1 year will be analysed in the same manner as the primary outcome parameter. Operation time will be compared between the treatment groups using the independent samples t-test or the Mann-Whitney test, as appropriate. Functional outcome at the specified follow-up moments will be compared between the treatment groups using an independent samples t-test. In addition, the course of functional recovery over time will be compared using a linear mixed model with time, treatment and baseline characteristics as fixed effects, and patient as random effect. Missing data will be imputed using multiple imputation before testing the differences in the outcome parameters. *P*-values less than 0.05 will be considered statistically significant.

The economic evaluation will compare differences in societal costs, as described in the paragraph ‘Study parameters’, to differences in quality adjusted life years (QALYs). Utilities obtained from the EQ-5D-5L will be used to determine QALYs. The QALYs will be calculated from the area under the curve in a utility-time figure. The duration of the trial will be taken as the time-horizon. Group averages will be statistically compared using non-paired t-test and a net-benefit analysis will be used to compare costs to patient outcome. Results will be presented in a cost-effectiveness acceptability curve.

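### The primary model adjusts for centre only, for a poor stated reason; pre-specifying age and Garden type as well would cost almost nothing and may gain a little power

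*Protocol article*

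**What the plan says.** The Statistical analysis section compares one-year revision surgery between arms by logistic regression with centre as the only covariate. Centre is included because sites differ in their experience with the DLBP. Nothing else is included because "In literature there is no clear evidence of other covariates that have a strong or moderate association with the primary outcome". Centre is also the only stratification factor (Randomization section).

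The baseline paragraph under Secondary outcome parameters lists, among the items assessed at admission, "sex, date of birth, general health score (using the ASA classification), fracture type and side". Eligibility covers ages 18 to 65 and Garden III or IV, so both age and fracture type vary between patients and neither is stratified for.

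The same Statistical analysis section plans, for functional recovery, a "linear mixed model with time, treatment and baseline characteristics as fixed effects".

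**The concern.** The text does not leave the covariates to a later document. It makes a choice and gives a reason, and the reason applies the wrong test. A lack of clear published evidence for an association is not evidence that there is none. In a randomised trial the question is what is gained if a pre-specified covariate is prognostic, against what is lost if it is not. If the loss is close to nil, uncertainty about prognosis favours including the covariate.

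Two things are at stake, both modest. One is some power, in a trial sized at 80%. The other is the estimate from the one trial that will be run: with stratification by centre alone, age or Garden type may differ between arms by chance, and a centre-only estimate carries that difference. Because the trial is unblinded, a covariate set fixed in advance also avoids a later argument about whether to adjust.

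**Working it through.** **1. The plan's own figure.** Inputs from Sample size calculation: "we assumed a 30% failure rate for the DHS and 15% failure rate for the DLBP", "with alpha of 5% in a two-sided test", power 80%. With the pooled two-proportion formula and mean risk (0.30 + 0.15)/2 = 0.225:

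n = [1.96·√(2·0.225·0.775) + 0.842·√(0.30·0.70 + 0.15·0.85)]² / 0.15² = (1.157 + 0.489)² / 0.0225 ≈ 120.5, so 121 per group.

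This matches "For a power of 80% we need 121 patients per group to prove the superiority of the DLBP". Power is 80.2% at 121 per group and 83.8% at 133 if nobody is lost. The formula uses no covariate, so the stated power stands without any further adjustment.

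**2. Model size.** The allowance is that "up to 10% of the patients may be lost to follow up", so about 266 × 0.9 ≈ 240 patients are observed, with 240 × 0.225 = 54 expected events. Treatment plus five centre terms makes 6 parameters: 54/6 = 9 events per parameter. Adding age and Garden type gives 54/8 ≈ 6.8; one further ASA term gives 54/9 = 6.

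**3. Power with and without adjustment.** The article gives no odds ratio for age, Garden type or ASA class against revision, so those below are assumptions. Simulated trials had 6 centres and marginal risks of 30% v 15%. The first two adjusted columns use 240 patients and Wald tests. They add age, Garden type and a pure-noise covariate: one noise term in the first (4000 trials per setting), a three-level noise ASA class in the second (3000 trials).

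| Assumed OR: per SD of age; Garden IV v III | Centre only → adjusted, one noise term | Centre only → adjusted, three-level noise ASA |
|---|---|---|
| 1.0; 1.0 | 0.80 → 0.80 | 0.81 → 0.80 |
| 1.5; 2.0 | 0.81 → 0.82 | 0.79 → 0.81 |
| 1.7; 2.5 | 0.81 → 0.84 | 0.80 → 0.83 |
| 2.0; 3.0 | 0.80 → 0.84 | 0.80 → 0.84 |

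A separate simulation used likelihood-ratio tests with 242 patients and one common odds ratio for age (per 2 SD), Garden IV (50% of patients) and high ASA class (20%). Power went from 80.3% to 80.5% at OR 1.0, 80.7% to 80.4% at 1.5, 81.4% to 82.7% at 2.0, and 81.2% to 85.0% at 3.0. With age as the only prognostic factor, the change was 0.0 points at 1.25 per SD and +1.0 at 1.45. With 1.5 per SD of age and 1.5 to 2.0 for Garden IV, it was about +1.4.

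The Monte Carlo standard error of a power figure is about 0.7 points (√(0.8·0.2/3000) = 0.007). The models in the table and in the likelihood-ratio run carry at least one term more than the two proposed below.

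**4. Type I error.** It was 0.049 to 0.051 and 0.049 to 0.059 in the two Wald settings of the table. With likelihood-ratio tests it was 0.055 to 0.063, equally for the centre-only and the adjusted model. Adjustment had no consistent effect on it.

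**5. Chance imbalance.** Assume Garden IV in half the patients and 121 per arm. The standard error of the difference in proportions is √(2·0.25/121) = 0.064. A gap of 10 points or more is 0.10/0.064 ≈ 1.56 standard errors, which occurs in about 12% of trials. To first order, such a gap shifts the log odds ratio by 0.10·ln 2.0 = 0.069 if the Garden odds ratio is 2.0, or by 0.10·ln 3.0 = 0.110 if it is 3.0. The planned odds ratio is (0.15/0.85)/(0.30/0.70) = 0.41, so an unfavourable gap would move it to about 0.44 or 0.46.

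**The case against.** The strongest reply is that nothing here is broken. Randomisation stratified by centre, with a pre-specified model that adjusts for centre, is a valid design. Its type I error already allows for chance imbalance in other variables. Choosing further covariates is a matter of judgement, and the authors state theirs. This stands, and it limits the point to efficiency.

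A reader might go further and infer that the trial gives up power. The documents do not support that. A loss requires age, Garden type or ASA class to be prognostic for revision, and the article gives no figure showing that any of them is. With no association the simulated power is the same either way.

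A reader might also infer an age effect from 13.2% failure at 60 or younger beside "Analysis of our data showed a failure rate of 15% for the DLBP in patients of 65 years and younger". These come from different data sets, one published and one not, and nothing says that one contains the other. Taking 13.2% of the 106 patients as 14 failures, the 95% Wilson interval is 8.0% to 21.0%, which includes 15%. The contrast carries no weight here.

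Nor does the functional-recovery model show a contradiction. It concerns a repeated continuous score with a baseline measurement, and adjusting it does not oblige a binary model to follow.

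The objection that about 54 events cannot carry more terms is fair to raise, but the simulations show no measurable harm to power or type I error, even with four extra terms. One cost does stand: adding covariates to a logistic model changes the odds ratio to one conditional on those covariates, so it is no longer the quantity that the centre-only model estimates.

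**Conclusion.** The point holds as a modest improvement. The centre-only model is valid and the sample size does not rest on more, but the stated reason for excluding patient-level covariates is a poor one. Adjustment for age and Garden type is worth about 0 points of power if they are unrelated or weakly related to revision, and about 1 to 2 points at odds ratios of 1.5 per SD of age and 1.5 to 2.0 for Garden IV. It reaches about 4 points only under strong associations (2.0 and 3.0). It would also keep a chance imbalance in these variables out of the realised estimate. All of these sizes rest on assumed odds ratios and, for the imbalance, on an assumed even split of Garden types.

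**What to change.** Before any analysis by arm, replace the sentence that rules out other covariates with wording such as: *The primary logistic model contains treatment, centre, age (continuous) and Garden type (III or IV); the model with treatment and centre only is a sensitivity analysis. The marginal risk difference from the primary model is reported with the odds ratio.* ASA class may be added, with its grouping fixed in advance. The baseline list says only fracture type, so state that this means the Garden type graded on the admission radiograph. Because the binary secondary outcomes are to be analysed in the same manner, say whether the added terms apply to them too.

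The cost is a few lines of plan wording and a short calculation for the risk difference, with no new data. The downside is small: two more terms on about 54 expected events, and an odds ratio that is conditional on age and Garden type. Reporting the risk difference addresses the latter and keeps the result on the scale of the 30% v 15% used for the sample size.

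### Continuous secondary outcomes are tested without the stratification factor centre, and visit-wise iHOT-12 and QALYs without the admission score: a modest, avoidable loss of precision

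*Protocol article*

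**What the plan says.** The Randomization section has patients "randomized with a 1:1 allocation using a random block size, stratified for centre". The Statistical analysis section puts study centre in the logistic regression for revision surgery, because centres differ in how long they have used the DLBP. It treats the binary secondary outcomes the same way.

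The continuous outcomes get tests that take no covariate:

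- iHOT-12: "Functional outcome at the specified follow-up moments will be compared between the treatment groups using an independent samples t-test".
- Operation time: "Operation time will be compared between the treatment groups using the independent samples t-test or the Mann-Whitney test, as appropriate".
- Costs and QALYs: "Group averages will be statistically compared using non-paired t-test". A net-benefit analysis follows, with no covariates described.

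For iHOT-12 the same section adds a linear mixed model for the course of recovery. Its fixed effects are time, treatment and baseline characteristics, with a random patient effect.

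Under Study parameters, iHOT-12 and EQ-5D-5L are completed during admission and at four follow-up points to 12 months. The cost questionnaire starts at 6 weeks. Operation time has no baseline value.

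**The concern.** Stratifying by centre balances the arms within each centre, so differences between centres largely cancel from the treatment contrast. A two-sample t-test still counts those differences as noise, and its standard error is then larger than the real sampling variation. The plan recognises centre as a relevant source of variation for its binary outcomes, yet drops it for the continuous ones.

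For iHOT-12 and QALYs there is a second source of precision, the admission score, which these tests do not use. Admission utility is also the first point of the QALY area under the curve, so a chance difference at baseline enters the QALY difference directly.

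Function and cost-effectiveness are declared secondary objectives, and the article gives no power for either. What is at stake is the width of their confidence intervals.

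**Working it through.** **The plan's own figure.** The sample size concerns the primary outcome: "we assumed a 30% failure rate for the DHS and 15% failure rate for the DLBP", "with alpha of 5% in a two-sided test". With pooled variance and no continuity correction:

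n = [1.96·√(2·0.225·0.775) + 0.8416·√(0.30·0.70 + 0.15·0.85)]² / 0.15² = (1.157 + 0.489)² / 0.0225 ≈ 120.5, hence 121.

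This matches "For a power of 80% we need 121 patients per group". The stated total follows from 121 × 1.10 = 133.1, taken as 133 per group or 266 in all. Dividing by 0.90 would give 135 per group, or 270, which is within 3%. None of this depends on how the continuous outcomes are analysed.

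**Inputs for the continuous outcomes.** The article gives no SD, ICC or baseline correlation for them. The following are therefore assumptions:

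- ICC, the share of outcome variance lying between centres: 0 to 0.10.
- ρ, the within-centre correlation of admission score with follow-up: 0 to 0.5.
- Reference effect: 0.36 SD, for which a t-test has 80% power at 121 per group, since 2.80 × √(2/121) = 0.36.

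**Centre only** (all that is available for operation time and costs). The ratio of adjusted to t-test standard error is √(1 − ICC), and the t-test's excess is 1/√(1 − ICC) − 1.

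| ICC | SE ratio | t-test SE too large by | Power after adjustment |
|---|---|---|---|
| 0 | 1.000 | 0% | 80% |
| 0.02 | 0.990 | 1.0% | 81% |
| 0.05 | 0.975 | 2.6% | 82% |
| 0.10 | 0.949 | 5.4% | 84% |

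**Baseline score** (iHOT-12 and QALYs only). The confidence-interval ratio for baseline alone is √(1 − ρ²). With centre as well it is √[(1 − ICC)(1 − ρ²)].

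| ρ | Baseline alone | CI narrower by | With centre, ICC 0.05 | Power, both |
|---|---|---|---|---|
| 0.1 | 0.995 | 0.5% | 0.970 | 82% |
| 0.3 | 0.954 | 4.6% | 0.930 | 85% |
| 0.5 | 0.866 | 13.4% | 0.844 | 91% |

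**Direct route into QALYs.** With straight lines between visits, the admission utility carries weight ½ × 6/52 = 0.058 years. A chance baseline difference therefore passes into the QALY difference at about 6% of its size, apart from its correlation with later utilities.

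**Check by simulation.** There were 4,000 trials per setting, with 242 patients in six centres of assumed sizes 60, 50, 45, 40, 30 and 17, and permuted blocks of 2, 4 or 6 within centre. There was no true difference unless stated.

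- ICC 0.05: the t-test reported a mean SE of 0.1277 against a true sampling SD of 0.123-0.124. Type I error was 0.040.
- ICC 0.10: 0.127 against 0.121-0.122. Type I error was 0.042.
- ICC 0: type I error was 0.045. Adjustment widened the SE from 0.1283 to 0.1286, or 0.2%, so little is lost when there is nothing to gain.
- ICC 0.05, ρ 0.5: adjustment cut the mean SE from 0.128 to 0.109. With a true difference of 0.36 SD, power rose from 79% to 90%.

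The simulation error of the type I rates is about 0.003. They show that the t-test does not exceed 5%, but do not fix exactly how conservative it is. With six unequal centres the SE reduction from centre was somewhat smaller than the formula gives: 0.1277 to 0.1254 (1.8%) at ICC 0.05, and 0.1272 to 0.1222 (4.0%) at ICC 0.10.

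**The case against.** The strongest reply is that iHOT-12 already has an adjusted analysis, the mixed model, and that an article may leave its covariate list to the analysis plan. It would be wrong to say that function is compared only by unadjusted tests. But the model is stated as an addition and leaves the visit-wise t-tests in place. Centre is not among its listed effects. Nor is the admission iHOT-12 clearly one of its baseline characteristics: the baseline parameters under Study parameters are items such as sex, ASA class, fracture type and BMI, and Table 1 gives questionnaires a separate row. The model does not touch operation time, costs or QALYs.

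Other parts of the reply stand and limit the point:

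- Operation time and costs have no baseline score, so only the small gain from centre is open to them.
- If operation time is analysed by Mann-Whitney, the standard-error formula does not apply.
- Costs and QALYs also enter a net-benefit analysis, so the cost-effectiveness conclusion is not shown to rest on the t-test.
- Differing DLBP experience would mainly lengthen DLBP operations in new centres, which is a treatment-by-centre interaction. If these take d minutes longer in half the centres, the pooled within-arm variance rises by d²/8, and an additive centre term removes d²/16, half of it.
- Chance baseline differences are ordinary sampling error, covered by the confidence interval. They are not bias.

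**Conclusion.** The point holds as a modest gain in efficiency on secondary outcomes. The plan adjusts its binary outcomes for the stratification factor but not the visit-wise iHOT-12 tests, operation time, costs or QALYs. For two of these it also leaves a collected baseline score unused.

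The size rests on assumptions: about 1-5% of the standard error from centre for an ICC of 0.02-0.10, and about 0.5-13% of confidence-interval width from the admission score for ρ of 0.1-0.5. If both are zero there is no gain. The admission scores are taken after the fracture, so ρ may well be low.

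A reader might infer that the t-tests are invalid or biased. Nothing in the plan supports that: they remain valid and, if centres differ, slightly conservative. A reader might also take a large saving as established, since ρ = 0.5 corresponds to 1/(1 − 0.25) = 1.33, a third more patients. The article gives no correlation or ICC from which to claim it. The primary analysis, the binary secondary outcomes and the sample size are unaffected.

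**What to change.** Change the Statistical analysis wording as follows:

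- **iHOT-12:** take the visit-wise contrasts from the planned mixed model, with baseline iHOT-12 and centre stated as covariates and a treatment-by-time term so that each visit has its own contrast. ANCOVA at each visit with the same two covariates would also serve.
- **QALYs:** regress on treatment, baseline utility and centre.
- **Costs and operation time:** regress on treatment and centre. If operation time is log-transformed, state that the estimate becomes a ratio of geometric means and no longer a difference in mean minutes.
- **Net-benefit analysis:** run it as a regression carrying the same covariates.
- **t-tests:** keep them, if wanted, as descriptive checks.

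The cost is wording only. The data are already collected, the planned software can fit these models, and no patients or visits are added. The one consequence to declare is the changed estimate if a log scale is used.
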